### Termination

2.6

Intervention may be concluded at an appropriate juncture based on the following circumstances: (i) patients who experience serious adverse events (SAEs) during treatment, including but not limited to tinnitus, dizziness, headache, localized discomfort at the site of irritation, or seizures; (ii) patients who request termination for reasons unrelated to the treatment; (iii) patients who identify a significant disease that was not previously detected before the initiation of treatment, or who develop other emerging health issues during the treatment process; (iv) upon the completion of all scheduled treatments.

Throughout the treatment process, we will implement health education for patients and their families, while accommodating treatment schedules to minimize disruptions to their daily lives. Additionally, we will prioritize patient feedback to enhance their trust, thereby improving adherence to the treatment regimen.

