#### Secondary outcomes

2.7.2

The secondary outcomes encompassed the mean changes in tremor power, amplitude, and frequency as recorded by accelerometers, in addition to the adherence rate and the incidence rate of SAEs.

During the 10-day stimulation period, a delay of up to 2 days will be permissible. Participants who experience a delay exceeding 2 days but less than 10 days will be classified as noncompliant. The compliance rate is defined as the percentage of participants who complete the 10-day stimulation within a maximum of 12 days. A high adherence rate suggests that the patient has completed the entire course of treatment punctually and indicating greater feasibility of the intervention.

Adverse event (AE) is defined as any adverse medical occurrence that occurs in an individual during clinical research, irrespective of whether it is attributable to medication or intervention. SAEs can lead to fatal outcomes for patients. A lower rate of SAEs indicates a higher level of safety associated with the intervention. A SAE is specifically defined as an event that results in one of the following outcomes for a participant: death, life-threatening conditions, hospitalization, disability, or permanent damage or necessitates intervention to avert permanent impairment or damage (in the case of devices), as well as other significant medical events.

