### Sample size

2.8

This pilot study involves a small number of patients and aims to assess the practicality and feasibility of the methodologies intended for use in a subsequent, larger, and more comprehensive investigation, as well as to identify any unforeseen challenges. Badran (46) indicated that a sample size of five patients per group is sufficient to ascertain whether a larger multicenter trial should be pursued. Additionally, Popa (29) proposed that 11 participants per group are adequate for evaluating feasibility in a pilot study. Drawing on prior research (28), our objective is to recruit eight patients per group. The findings of this study are expected to provide preliminary insights into the safety and feasibility of dual-target TMS in patients with ET and will inform the estimation of sample size and the conduct of a power calculation for the planning of a Phase 3 trial.

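### The stopping rule in Section 2.6 lists headache, dizziness, tinnitus and local discomfort as SAEs, contrary to the consequence-based SAE definition in Section 2.7.2

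*Protocol article*

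**What the plan says.** Section 2.6 (Termination) opens permissively: "Intervention may be concluded at an appropriate juncture based on the following circumstances". Its first circumstance is a patient who has "serious adverse events (SAEs) during treatment, including but not limited to tinnitus, dizziness, headache, localized discomfort at the site of irritation, or seizures". The abbreviation is the one used for the outcome, and the symptoms are presented as members of that class.

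Section 2.7.2 (Secondary outcomes) keeps two terms apart. The broad one is: "Adverse event (AE) is defined as any adverse medical occurrence that occurs in an individual during clinical research". The narrow one is tied to consequences: "A SAE is specifically defined as an event that results in one of the following outcomes for a participant". The consequences listed are death, threat to life, hospital admission, disability, and permanent damage or action needed to prevent it. The list closes with a catch-all, "as well as other significant medical events".

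The same section names the secondary outcomes. After the accelerometer measures it adds safety and feasibility: "in addition to the adherence rate and the incidence rate of SAEs". It also states how the safety result is to be read: "A lower rate of SAEs indicates a higher level of safety associated with the intervention". No rate of non-serious adverse events is listed as an outcome.

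**The concern.** One abbreviation is used in two ways. Section 2.6 identifies SAEs by symptom; Section 2.7.2 identifies them by what happens to the patient. A passing headache or some soreness at the coil site is an SAE under the first and an ordinary adverse event under the second.

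This would matter little if SAEs only triggered a stopping decision. However, SAE incidence is the sole named safety outcome, and the article reads a lower rate directly as greater safety. Section 2.8 adds that the study should give preliminary information on safety ahead of a Phase 3 trial. The symptoms concerned are also foreseeable: Section 4 (Safety monitoring) names most of them among the expected effects of TMS. Staff who take the Section 2.6 list as guidance on what an SAE is could therefore enter non-serious events into the SAE count.

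**Working it through.** **Comparison of the texts.** The plan states no figure to reproduce, so the check begins with the wording.

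| Event, with no further consequence | Section 2.6 (i) | Section 2.7.2 |
|---|---|---|
| Tinnitus | SAE | Not an SAE by name alone |
| Dizziness | SAE | Not an SAE by name alone |
| Headache | SAE | Not an SAE by name alone |
| Discomfort at the coil site | SAE | Not an SAE by name alone |
| Seizure | SAE | Can qualify |

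Four of the five examples are classified differently. The seizure is not part of the conflict.

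**Scale.** The input is the planned arm size in Section 2.8: "our objective is to recruit eight patients per group". If one more patient in an arm of size n is counted as having an SAE, the arm's rate rises by 100/n percentage points.

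- n = 8: 100/8 = 12.5 points.
- 0 of 8 has an exact (Clopper-Pearson) 95% confidence interval of 0% to 36.9%. The upper limit is 1 − 0.025^(1/8) = 0.369.
- 1 of 8 is 12.5%, with exact 95% interval 0.3% to 52.7%. The lower limit is 1 − 0.975^(1/8) = 0.003. The upper limit is the p that solves (1 − p)^8 + 8p(1 − p)^7 = 0.025, which is 0.527.

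**Arms need not be 8.** Section 2.9 uses simple randomization, so arm sizes vary. Assume 24 patients, each with probability 1/3 of a given arm, so that arm size is Binomial(24, 1/3).

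- P(exactly 8) = C(24, 8) × (1/3)^8 × (2/3)^16 = 0.171.
- P(4 to 12) = 0.952.
- Step at n = 4: 100/4 = 25 points. Step at n = 12: 100/12 = 8.3 points.

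Section 2.9 assigns arms by the remainder of a two-digit number divided by three. If these numbers run from 00 to 99, the probabilities are 34%, 33% and 33%, and P(4 to 12) is 0.950 or 0.952. The range is unchanged.

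**What cannot be computed.** The article gives no rate for these symptoms and no indication of how staff would code them, so no frequency of misclassification can be derived.

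**The case against.** The strongest defence is that the Section 2.6 list is governed by the word serious and means serious instances of these symptoms. A headache or dizziness that leads to hospital admission is an SAE under Section 2.7.2, and the catch-all there is broad. On this view one section lists kinds of event and the other lists criteria of seriousness, and they do not collide. The reading is possible but strained. The sentence does not say it, and it fits discomfort at the coil site poorly. Section 4 also calls headache, local discomfort and tinnitus plain adverse events, to be managed by stopping treatment, observation and analgesics if needed.

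A second defence is that the outcome is defined where it is named, in Section 2.7.2, and that Section 2.6 only permits stopping and classifies nothing for analysis. This largely stands: no passage makes Section 2.6 govern the SAE count. Equally, none says that its list is to be ignored when SAEs are counted.

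Third, Section 4 requires severity, duration, measures taken and treatment outcome to be recorded for every event, so a wrongly labelled event can be reclassified. This stands and limits the consequence.

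Fourth, the step of 12.5 points is a property of any yes/no outcome in an arm of eight, and the article names no between-arm test of SAEs that it would alter. This is also correct. The figures show what one miscoded patient does to the reported rate; they are not evidence that miscoding will occur.

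Finally, a condensed article may leave event-coding rules to the full protocol. That would explain a missing detail. It does not explain two printed statements that disagree.

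**Conclusion.** The concern holds: Section 2.6 (i) is wrong as written. It presents four symptoms as SAEs that do not meet the Section 2.7.2 definition by name alone, and that definition underlies the only named safety outcome.

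The severity is minor. Each patient affected would move an arm's SAE rate by 12.5 points at the planned arm size, or by 25 to 8.3 points for arms of 4 to 12. That range assumes 24 patients and equal assignment probabilities. The number of patients affected is unknown, and the recorded event details would allow correction. The primary outcome, adherence and unblinding are not affected, and Section 4 is not part of the contradiction.

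**What to change.** Two short edits are enough.

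- In Section 2.7.2, add a clause stating that the definition there is the only one used to count SAEs for the outcome.
- Reword Section 2.6 (i) along these lines: *SAEs as defined in Section 2.7.2, or adverse events that are intolerable or require stopping (e.g. tinnitus, dizziness, headache, localized discomfort, seizures)*.

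This keeps the investigator's freedom to stop treatment for a non-serious but intolerable event and keeps such events out of the SAE rate. The cost is one phrase and one clause, with no new data, procedure or analysis and no change to Section 4. Section 2.1 reports that recruitment was still under way at submission, so clarifying now is better than reclassifying events after data collection.

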### Outcome measurement

2.7

#### Primary outcome

2.7.1

The primary outcome measure will be the mean change from baseline over the course of 4 weeks (at days 1, 5, 10, D10-24 h, then at weeks 1, 2, 3, and 4). This assessment will focus on the average tremor score derived from the TETRAS. The TETRAS (45) is a widely utilized instrument for evaluating the severity of ET and is employed to assess the remission and recovery of ET following TMS. The scale comprises a 12-item section that evaluates activities of daily living and a 9-item section that assesses tremor severity. Each item is rated on a scale from 0 to 4, with higher scores indicating greater severity.

#### Secondary outcomes

2.7.2

The secondary outcomes encompassed the mean changes in tremor power, amplitude, and frequency as recorded by accelerometers, in addition to the adherence rate and the incidence rate of SAEs.

During the 10-day stimulation period, a delay of up to 2 days will be permissible. Participants who experience a delay exceeding 2 days but less than 10 days will be classified as noncompliant. The compliance rate is defined as the percentage of participants who complete the 10-day stimulation within a maximum of 12 days. A high adherence rate suggests that the patient has completed the entire course of treatment punctually and indicating greater feasibility of the intervention.

Adverse event (AE) is defined as any adverse medical occurrence that occurs in an individual during clinical research, irrespective of whether it is attributable to medication or intervention. SAEs can lead to fatal outcomes for patients. A lower rate of SAEs indicates a higher level of safety associated with the intervention. A SAE is specifically defined as an event that results in one of the following outcomes for a participant: death, life-threatening conditions, hospitalization, disability, or permanent damage or necessitates intervention to avert permanent impairment or damage (in the case of devices), as well as other significant medical events.

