### Study design

2.1

This is a Phase 2 clinical trial designed to evaluate the efficacy and safety of dual-target TMS for the treatment of ET. The study is randomized and controlled, incorporating blinding for both patients and assessors. Patients will be screened for study participation within study enrollment. All participants will be evaluated via neurological examination, The Essential Tremor Rating Assessment Scale (TETRAS), electromyographic and accelerometric recording, and magnetic resonance imaging (MRI). The participants will be then randomly assigned to one of three groups: dual-target stimulation group, single-target stimulation group or sham stimulation group. We will examine the patients’ vital signs before and after each day of treatment and record daily treatment completion and adverse event occurrence. Electrophysiological detection and TETRAS will be performed at baseline, after the first, fifth, tenth day of treatment (D1, 5, 10), 24 h after 10 days of treatment (D10-24 h), and at 1, 2, 3 and 4 weeks (W1, 2, 3, 4) after stimulation.

MRI will be carried out at baseline, D10, and W4 (Table 1). Recruitment for this study is ongoing at the time of submission.

**Table 1 tab1:** Study schedule.

Procedure	Screening	Treatment				End	Follow-up			
Time point	D 0	D1-B	D1-A	D5-A	D10-A	D10-24 h	W1	W2	W3	W4
Basic										
Demography	✓									
Eligibility	✓									
Vital signs	✓	↔				✓	✓	✓	✓	✓
Informed consent	✓	↔				✓	✓	✓	✓	✓
Assessment										
TRETRAS		✓	✓	✓	✓	✓	✓	✓	✓	✓
Tremor analysis		✓	✓	✓	✓	✓	✓	✓	✓	✓
MRI	✓				✓					✓
Trial evaluation										
Adverse event			↔			✓	✓	✓	✓	✓
Safety evaluation			↔			✓	✓	✓	✓	✓

TRETRAS, The Essential Tremor Rating Assessment Scale; MRI, Magnetic Resonance Imaging; D0, Days before treatment; D1-B, Before the first day of treatment; D1-A, After the first day of treatment; D5-A, After 5 days of treatment; D10-A, after 10 days of treatment; D10-24 h, 24 h after 10 days of treatment; W1, One week after treatment completion; W2, Two weeks after treatment completion; W3, Three weeks after treatment completion; W4, Four weeks after treatment completion.

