## Safety monitoring

4

Prior to the experiment, investigators will inform all enrolled patients of the possible benefits and risks and have them sign an informed consent form.

TMS may lead to adverse events, including headache, localized discomfort at the stimulation site, hearing loss, tinnitus, seizures, and syncope. Consequently, several preventive measures are recommended: the use of earplugs during TMS therapy, discontinuation of treatment in the event of headache or localized discomfort, careful monitoring of symptom changes, and the administration of analgesics as needed. Although epileptic seizures are rare during TMS, if seizures or syncope occur, it is imperative to immediately cease stimulation, assess the patient’s vital signs, and conduct further medical evaluations after the seizure has resolved. In instances of discomfort during the procedure, treatment should be halted immediately, followed by clinical observation and symptomatic management (47).

The Ethics Committee of the First Affiliated Hospital of Xi’an Jiaotong University will oversee the safety of this study and provide guidance as needed. In the event of an adverse occurrence, subjects must receive prompt medical attention. Detailed documentation of the adverse event—including its name, time of occurrence, duration, severity, therapeutic measures undertaken, and treatment outcomes—should be meticulously recorded and reported to the Research Safety Supervisory Committee in a timely manner. If necessary, blinding procedures will be implemented in accordance with established protocols. The attending physician will evaluate the causal relationship between the treatment interventions and any adverse outcomes, and will determine whether the patient should continue with follow-up treatment based on the specific circumstances.

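### The only declared safety outcome is SAE incidence, which says little about safety with about 8 patients per arm and is defined in two conflicting ways

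*Protocol article*

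**What the plan says.** **Declared outcome.** Section 2.7.2 (Secondary outcomes) names changes in accelerometer measures, "in addition to the adherence rate and the incidence rate of SAEs". No other safety item appears among the primary, secondary or exploratory outcomes. The same section says how the result is to be read: "A lower rate of SAEs indicates a higher level of safety associated with the intervention".

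**What counts as serious.** Section 2.7.2 defines an SAE by its consequence: "death, life-threatening conditions, hospitalization, disability, or permanent damage or necessitates intervention to avert permanent impairment or damage", followed by a residual category for other significant medical events. Section 2.6 (Termination) speaks instead of "serious adverse events (SAEs) during treatment, including but not limited to tinnitus, dizziness, headache, localized discomfort at the site of irritation, or seizures".

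**Adverse events in general.** Section 2.7.2 defines them ("Adverse event (AE) is defined as any adverse medical occurrence that occurs in an individual during clinical research") but does not make them an outcome. Section 2.1 says the team will "record daily treatment completion and adverse event occurrence", and Table 1 continues adverse-event recording through week 4. Section 4 (Safety monitoring) names the expected effects, "TMS may lead to adverse events, including headache, localized discomfort at the stimulation site, hearing loss, tinnitus, seizures, and syncope", describes seizures as rare, and requires each event to be documented, "including its name, time of occurrence, duration, severity, therapeutic measures undertaken, and treatment outcomes".

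**Analysis and size.** Section 5 plans safety analyses in everyone who had at least one TMS session, without naming the variables. Section 2.8 aims for eight patients per group.

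**The concern.** Safety is a lead aim of the trial and part of its hypothesis, and section 2.8 wants the results to inform a Phase 3 trial. The one outcome chosen to carry that aim counts a kind of event that a sample this small is poorly placed to measure. The events most likely to describe tolerability are recorded but sit outside the outcome list.

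The gap matters because sections 2.6 and 4 both treat effects such as headache and local discomfort as possible reasons to stop treatment. Under the criteria in section 2.7.2, such an event could end a patient's stimulation and still leave no trace in the safety outcome.

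The interpretive sentence makes this worse. Read literally, zero events in an arm of eight is the best safety result obtainable, yet nothing in the plan says how high a true rate that result leaves open.

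**Working it through.** **Inputs from the document:** 8 patients per group (section 2.8); 24 patients in three groups (Abstract, Methods). The plan's own total reproduces: 3 × 8 = 24. It is not a power calculation, and no SAE rate or safety precision is stated.

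**1. What zero events can exclude.** The exact (Clopper-Pearson) two-sided 95% upper limit for 0 of n is 1 − 0.025^(1/n). No assumed event rate is needed.

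| Patients | Calculation | Upper limit |
|---|---|---|
| One arm, 8 | 1 − 0.025^(1/8) | 36.9% |
| Both active arms, 16 | 1 − 0.025^(1/16) | 20.6% |
| All, 24 | 1 − 0.025^(1/24) | 14.2% |

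With one-sided 95% limits, 1 − 0.05^(1/n), the figures are 31.2%, 17.1% and 11.7%.

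**2. How likely a zero count is.** The chance of no SAE in 24 patients is (1 − p)^24. The document gives no p, so these values are assumptions.

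| Assumed SAE risk per patient | Chance of zero in 24 |
|---|---|
| 0.5% | 89% |
| 1% | 79% |
| 2% | 62% |
| 5% | 29% |
| 10% | 8% |

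Zero is the likelier result only when p is below 1 − 0.5^(1/24) = 2.8%.

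**3. Dependence on the definition.** If the effects listed in section 2.6 count as SAEs and occur in an assumed 20% of patients, the chance of zero in 24 is 0.8^24 = 0.5%; at 30% it is lower still. The same outcome could thus be almost always zero or almost never zero, depending on which section governs.

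**4. What an outcome based on all adverse events would add.** The chance of at least one affected patient in an arm of 8 is 1 − (1 − p)^8. For assumed rates of 10%, 20% and 30% this is 57%, 83% and 94%.

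**5. What it would not add.** With 8 v 8 and a two-sided Fisher exact test at 0.05, 5/8 v 0/8 is needed for significance (p = 0.026; 4/8 v 0/8 gives p = 0.077). Power is about 3% for 30% v 10%, 22% for 50% v 10% and 39% for 60% v 10%. Such an outcome describes the arms; it does not test them.

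**The case against.** A reader might infer that the SAE count will probably be zero in every arm. The document does not support that. It gives no SAE rate, the inference needs a true rate below about 2.8%, and it fails if section 2.6 governs. Even section 2.7.2 has its residual category, so a seizure, syncope or lasting hearing loss could count.

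A reader might also infer that the trial would declare the intervention safe by default. That goes too far as well. No rule for declaring safety is stated, section 2.8 calls the expected insights preliminary, and section 5 plans safety analyses without confining them to SAEs. Adverse-event tables may well be intended, and their layout is the kind of detail an article leaves to a fuller document.

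The adherence rate, also a secondary outcome, is a partial proxy for tolerability, since an event that ends stimulation or delays it too long would lower it. But it misses short interruptions and does not separate stopping for side effects from stopping for unrelated reasons.

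Finally, an outcome covering all adverse events could not reliably separate arms of eight either, as step 5 shows.

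All of this limits the point without removing it. The choice of SAE incidence as the sole safety outcome, the unbounded reading attached to it and the two conflicting accounts of an SAE are stated in the text; they are not omissions from a condensed article.

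**Conclusion.** The point holds as a weakness in the declared outcome and its stated interpretation. SAE incidence alone is a poor safety outcome at this size: zero events leaves a true rate of up to 37% open in one arm and 14% across all 24 patients. These limits rest only on the planned numbers; arms that differ from eight would have different limits. Under the criteria in section 2.7.2, most of the expected TMS effects would normally go uncounted.

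Sections 2.6 and 2.7.2 contradict each other on what an SAE is, and that decides what the outcome measures. The probabilities for zero counts and for adverse events rest on assumed rates and only illustrate the point. The sponsor should make the change, since it affects how the safety aim is answered and requires no new data.

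**What to change.** 1. Reconcile sections 2.6 and 2.7.2 so that a single SAE definition applies throughout.
2. Add to section 2.7.2 a descriptive safety outcome: per arm, the proportion of patients with any adverse event and the proportion with an adverse event that interrupts or ends stimulation. Tabulate by type, including the effects named in section 4, and by severity, with exact 95% intervals.
3. Keep SAEs as a separate line under the reconciled definition, also with exact intervals.
4. Replace the sentence equating a lower SAE rate with greater safety by a statement of what the observed count can exclude. For example, zero of 8 excludes only true rates above 37% at the two-sided 95% level.
5. State that comparisons of adverse events between arms are descriptive and not powered.

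The cost is some wording and one table, since section 2.1, Table 1 and section 4 already provide for collecting the data. The downside is that the resulting safety statement will be less favourable.
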